### Interventions

2.8

#### Nature of intervention

2.8.1

This study tested whether the content of an email invitation—specifically, the inclusion of an incentive framing—affected recipients' willingness to register interest in a future smartphone-based EMA assessment of well-being in and around King's Cross. Eligible users were contacted via email through the King's Cross Equiem database as part of a neighborhood public-engagement initiative delivered in collaboration with a university. Each participant received one of three email versions: (1) financial incentive, (2) social incentive, or (3) no-incentive control. All emails used identical formatting and core wording; they differed only in a single paragraph describing the incentive (or no paragraph for the control condition). An example invitation email is shown in Figure 2. The condition-specific paragraph used in each trial arm in the first email round is summarized in Table 4, and exact screenshot examples from all trial arms across both email rounds are provided in Supplementary File S2. A second round of reminder emails was subsequently disseminated using revised wording and design while maintaining the arm-specific incentive framing. Full email materials are provided in Supplementary File S2.

**Figure 2 F2:**
[figure not shown]
Example invitation email screenshot from the financial incentive condition. **Note.** The bracketed label in the example screenshot (e.g., “[Visitors - EMAIL 1]”) appeared only in internal test emails used to verify resident-type versions before distribution and was not included in participant-facing emails. The bracketed text shown after hyperlinks (e.g., “[email.kingscross.community]”) is an artifact of the internal screenshot examples and was not part of the intended participant-facing email wording. Exact internal screenshot examples from all trial arms across both email rounds, including the revised second-round reminder emails, are provided in Supplementary File 2.

**Table 4 T4:** Condition-specific paragraph inserted into the invitation email for each trial arm in the first email round.

**Email component**	**Financial incentive condition**	**Social incentive condition**	**No incentive condition**
**Round 1: condition-specific paragraph**	If you were selected to take part in this research, you would have the opportunity to enter an exciting prize draw, with a chance to win one of four £100 shopping vouchers in a shop of your choice in King’s Cross or Coal Drops Yard.	If you were selected to take part in this research, you would have the opportunity to join the research team for an on-site social event in King’s Cross to discuss the research findings and meet with other participants.	No additional condition-specific paragraph.

The invitation described that the future EMA study would involve brief smartphone questionnaires about daily experiences in and around King's Cross, delivered multiple times per day over a two-week period. Recipients indicated willingness to participate via one of two embedded response options (Yes/No), each linking to a short follow-up questionnaire where responses were recorded securely.

In the financial incentive condition, the email stated that individuals selected for the future EMA study would be entered into a prize draw to win one of four £100 shopping vouchers redeemable at King's Cross or Coal Drops Yard. In the social incentive condition, the email stated that selected participants would be invited to an exclusive post-study event with other participants and researchers to discuss findings. The control condition included no incentive text.

To support participation, a single reminder email was sent to non-responders; the reminder maintained the same condition-specific incentive paragraph and call-to-action links, while using a brief reminder-oriented opening. The reminder email text is provided in Supplementary File S2.

#### Delivery of intervention

2.8.2

The intervention emails were sent from the official email address of the King's Cross neighborhood's asset manager, The King's Cross Group, a familiar and trusted source for recipients due to their prior engagement with community communications (see Supplementary File S2). Successful email delivery was confirmed through the platform's delivery reports, and each participant received the intervention email twice: an initial email and a follow-up reminder.

The initial emails were disseminated on September 12, 2024, followed by a single reminder email sent one month later, on October 17, 2024; the participation survey link remained open until November 30, 2024. The need for a potential third reminder was evaluated; however, an additional round was not undertaken as it was deemed unnecessary. A one-time in-app smartphone notification to non-responders (linking to the same landing page) was also considered but not implemented to maintain email as the sole standardized delivery channel across conditions. Adding an in-app prompt could have changed contact salience/dose and introduced uneven exposure (e.g., disabled notifications or inactive app use), potentially confounding incentive effects, and could increase perceived burden. This decision, together with the decision not to send a third reminder, was informed by unsubscribe patterns observed after the initial email round, suggesting that additional contact beyond the single scheduled reminder could increase disengagement from the platform's routine communications (i.e., opting out/unsubscribing), rather than disengagement from the study itself.

At each dissemination round, participants who had already responded to the binary participation question were excluded from subsequent mailings to avoid redundancy. This process was conducted by two designated staff members at Garden State, who removed responders from the mailing list before each distribution. Yet, an apology wording was included in the reminder email as a courtesy fail-safe in the event that any prior responder received a reminder despite list cleaning. The reminder email differed only in the subject line and opening paragraph; all condition-specific content remained unchanged. All reminder emails were scheduled for delivery at 2:00 p.m. on the designated dates, based on prior communication analytics from The King's Cross Group, which indicated high open rates at that time

### Study outcomes

2.9

#### Primary outcome variable

2.9.1

The primary outcome variable of this study is the willingness to participate in a future smartphone ecological momentary assessment (EMA) study. The variable is measured through a binary response included in the intervention email. Participants could select either “*Yes, I would like to register my interest!”* (coded as 1) or “*No, I am not interested!”* (coded as 0). Operationally, “Yes” would be defined as completing the core demographic/residential relationship items and submitting a valid email address to register interest; “No” would be defined as selecting the non-interest option. Moreover, participants who did not respond to the invitation (i.e., did not click either option) would be coded as 0 (not willing) in the primary intention-to-treat analysis.

#### Secondary outcome variable

2.9.2

The study also assessed two secondary outcomes among participants who indicated that they were unwilling to participate in the EMA study. The first secondary outcome captured the reason for unwillingness to participate. Participants were asked to identify one or more factors influencing their decisions not to participate. These factors included (1 = “Inadequate compensation”), app notification frequency (2 = “Too many notifications”), study duration (3 = “long/excessive study duration”), limited time availability (4 = “daily time constraints”), app download (5 = “Reluctance to install new app”), privacy concerns (6 = “privacy and data security concerns”), lack of interest (7 = “Lack of interest in the study”), and [8 = Other reasons(please specify)]. Participants were asked to “select the main reason(s) for not participating in the future research study” from this list.

The second secondary outcome assessed alternative incentive preference. This outcome was obtained only for participants who selected “*Inadequate compensation”* as their main reason for non-participation. These participants were subsequently presented with a list of seven potential incentive alternatives they preferred to be offered for a similar study in the future. They were asked, “Would any of these increase your likelihood to participate? Check all that apply” The incentive options were: nothing (1 = “Nothing will increase my likelihood”), guaranteed cash payment (2 = “£50 guaranteed cash on study completion”), gift card (3 = “Gift card on study completion”), prize draw (4 = “4× £100 cash prize draw”), personalized feedback (5 = “Personalized well-being feedback”), special event invitation (6 = “Exclusive post-research social & feedback event”), charity donation (7 = “Donation to charity”), and other (8 = “Other—please specify”).

### Data collection

2.10.

Data for this study were collected through online questionnaires hosted on the Give My View (GMV) platform, which was the pre-existing data collection system available for the project and therefore informed the implementation approach. GMV is a public citizen digital engagement platform developed by LandTech to facilitate community participation and feedback. Accordingly, the capabilities and limitations of the GMV platform, together with the randomized design of the study, informed the development of two-stage questionnaire combinations.

The email invitation contained two response links (“Yes”/“No”), each directing recipients to a corresponding questionnaire. Those selecting “Yes” completed a brief sociodemographic questionnaire capturing demographic characteristics and indicators of study interest; those selecting “No” completed a brief questionnaire capturing reasons for non-participation and incentive preferences (see Supplementary File S1).

To ensure responses were correctly attributed to the participant's assigned incentive condition and user category, separate questionnaire instances were created for each combination of incentive condition (financial, social, no-incentive), response option (Yes/No), and user category (residents, visitors, commercial occupiers), yielding 18 instances in total. Each instance was linked via a condition-specific URL and labeled with a structured identifier to support tracking and analysis (e.g., RFNY=Resident–Financial Incentive–Yes; VNICN=Visitor–No Incentive–No).

### Data management

2.11.

Several procedures were implemented to uphold data quality and ensure data security. The GMV survey design required responses for four core demographic items (gender, ethnic group, age range, and relationship to King's Cross), while follow-up preference items were optional. Additionally, the platform's device recognition feature guaranteed that once a participant submitted a response, they were unable to access the survey again, thereby preserving the uniqueness of each submission. As data were collected directly in a pre-coded digital format on the GMV platform, manual data entry was unnecessary, reducing the risk of transcription errors and enhancing the overall accuracy of the dataset.

The primary outcome—the participant's binary decision to participate (“Yes” or “No”)—was derived directly from the raw data exported from the GMV platform. Each survey response was coded post-collection: responses from participants who completed the “Yes” survey were assigned a value of 1 and those who completed the “No” survey were assigned a value of 0. This coding process ensured consistent and accurate representation of the primary outcome for analysis.

All data storage, handling, and sharing procedures will comply with institutional data security and ethical guidelines. Study data will be cleaned and anonymised prior to any sharing. Access to identifiable and cleaned study data will be restricted to authorised members of the research team and approved project partners in accordance with prior data-sharing agreements.

### Analysis plan

2.12.

The trial will be reported in accordance with the CONSORT guidelines for reporting randomized trials. The detailed statistical analysis plan has been published elsewhere (34). All analyses will follow the intention-to-treat principle, including all randomized invitees, to ensure a comprehensive assessment of the intervention's effectiveness (35). The primary analysis will compare the effectiveness of the three intervention arms. Secondary analyses will explore subgroup differences in response to the incentives as well as examine barriers to participation and alternative preferences. Sensitivity analyses will be conducted to evaluate the robustness of the findings. The following sections outline these analyses in detail.

#### Primary outcome analysis

2.12.1.

The primary outcome is willingness to participate (Yes/No), operationalized as submission of a completed core questionnaire and valid email address (“Yes”) vs. not registering interest (selecting the non-interest option or not selecting either option). The effect of incentive type (financial, social, or no incentive) on willingness to participate will be evaluated using logistic regression. The model will include incentive condition as the main predictor and residential status (residents, workers, visitors) as a covariate, consistent with the stratification used during randomization. Odds ratios (OR) with 98.33% confidence intervals (CI) will be reported to compare each incentive group with the control group. A two-tailed *p*-value of < 0.01667 will be considered statistically significant (Bonferroni-adjusted to control the family-wise error rate at 0.05 across the three planned pairwise comparisons). In addition to odds ratios, marginal risk differences (RD) will be estimated to enhance interpretability.

Predicted probabilities will be obtained from the fitted logistic model through marginal standardization and RDs will be computed as the absolute difference in these marginal probabilities between groups. Confident Intervals (95%) will be derived using robust standard errors or nonparametric bootstrap methods, as appropriate. Primary inferences for the three pairwise comparisons of incentive type on the primary outcome will use 98.33% confident intervals (CIs) to adjust for multiple comparisons. Exploratory subgroup analyses and complementary RD estimates use 95% CIs and will be interpreted as estimation rather than confirmatory hypothesis testing. Interaction terms in subgroup models will be evaluated at a two-tailed alpha level of 0.05 and results will be reported as exploratory findings. In addition to the frequentist primary analysis, Bayes factors will be calculated to complement interpretation of the primary outcome by quantifying evidence for differences between incentive conditions.

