### Study design

2.1

This is a three-arm superiority randomised controlled trial (RCT) that evaluates the impact of two types of incentives against a control condition on willingness to participate in EMA research among an urban neighbourhood population.

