### Sample size

2.4

The sample size for this study was fixed at 4,809 individuals, representing the total number of users in the King's Cross Equiem database who met the eligibility criteria. Power analysis was conducted to evaluate the study's ability to detect differences between the three incentive conditions under varying levels of willingness to participate in the control group. Because the total N was fixed by the sampling frame, results are presented as minimum detectable differences (MDEs) in percentage points for each assumed control rate (29). Power for differences in proportions was calculated using standard two-sample methods for binary outcomes (30).

Due to limited directly comparable external estimates of baseline participation without incentives in similar digital-based recruitment contexts, a plausible range of control proportions (1%–70%) was assumed and used as a sensitivity analysis. Because EMA recruitment can yield single-digit participation rates in some settings (23), MDEs for low baseline proportions (1%–10%) are included within this range as part of the same fixed-N sensitivity framework. Power calculations were then conducted for each assumed proportion, using a Bonferroni-adjusted significance level of 0.01667 (0.05/3) to maintain a family-wise error rate of 0.05 across the three planned pairwise comparisons among the three conditions (31). Table 2 summarizes the assumptions and the corresponding minimum detectable differences.

**Table 2 T2:** Results of power analysis for detecting differences in willingness to participate across incentive conditions.

N	Proportion willing in control	Percentage point difference
4,809	0.01	1.16
4,809	0.02	1.53
4,809	0.03	1.81
4,809	0.04	2.04
4,809	0.05	2.24
4,809	0.06	2.41
4,809	0.07	2.57
4,809	0.08	2.72
4,809	0.09	2.85
4,809	0.10	2.97
4,809	0.20	3.86
4,809	0.30	4.36
4,809	0.40	4.61
4,809	0.50	4.66
4,809	0.60	4.52
4,809	0.70	4.18

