#### Sequence generation

2.7.1

Participants were randomized into three incentive groups (financial incentive, non-financial incentive, or no incentive) using a stratified block randomization procedure. Stratification was based on participant type within the Equiem communication platform (residents, visitors, and commercial occupiers). Randomization lists were generated using the Sealed Envelope online randomization service, which employed randomly permuted block sizes of 3, 6, and 9 to ensure a balanced allocation across incentive groups within each stratum. Sealed Envelope is a web-based clinical trial randomization platform that generates allocation sequences based on user-specified parameters (e.g., allocation ratio, stratification variables, and randomly permuted block sizes) and allows the sequence to be exported for implementation (33). The platform provides documentation on permuted-block and stratified randomization procedures, supporting transparent reporting and reproducible sequence generation. The randomization lists were generated by the researcher prior to participant assignment and without access to any identifying information (e.g., names or email addresses) stored on the Equiem platform.

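### Single-step Bonferroni over the three pairwise tests is valid but needlessly conservative: a step-down rule for three arms keeps 5% family-wise error, loses no rejection and gains power

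*Protocol article*

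**What the plan says.** The Sample size section sets the per-comparison level by "using a Bonferroni-adjusted significance level of 0.01667 (0.05/3) to maintain a family-wise error rate of 0.05 across the three planned pairwise comparisons". The Primary outcome analysis section repeats the rule: "A two-tailed *p*-value of < 0.01667 will be considered statistically significant", with the reason given as "Bonferroni-adjusted to control the family-wise error rate at 0.05 across the three planned pairwise comparisons". It reports odds ratios with 98.33% "confidence intervals (CI) will be reported to compare each incentive group with the control group", and then says that primary inferences for the three pairwise comparisons will use 98.33% intervals. Marginal risk differences get 95% intervals and are described as estimation. The article mentions no stepwise procedure.

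Total N is set by the sampling frame ("The sample size for this study was fixed at 4,809 individuals"), and allocation is balanced over three arms. The Sample size section claims approximately 80% power at the differences in Table 2.

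**The concern.** Each of the three tests stays at 0.01667 whatever the other two show. The three hypotheses are logically linked: control = financial and control = social together imply financial = social. It is therefore impossible for exactly one of the three equalities to be false. After one rejection, the error rate still reserved for the other two is larger than needed to protect the family at 5%.

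Objective 2 asks about each incentive against control, and N cannot be increased, so unused error rate is sensitivity lost on the primary question. The Sample size section itself warns that small effects may be missed if willingness is in single digits, and that null findings will be read against the minimum detectable differences.

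**Working it through.** **Inputs.** Three arms with balanced allocation (Study design; Sequence generation). N = 4,809 (Sample size), so 4,809 / 3 = 1,603 per arm. Two-tailed level 0.05 / 3 = 0.01667 (Primary outcome analysis), critical z = 2.394. Non-responders are coded 0 (Primary outcome variable), so nobody drops out of the denominator. Control rates and differences come from Table 2.

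**The plan's own figure first.** Power = Φ[(d − z·SE0) / SE1], where SE0 is the pooled and SE1 the unpooled standard error. For 30% vs 34.36%:

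- 4,809 / 2 = 2,404.5 per arm: SE0 = 0.01347, SE1 = 0.01346; (0.0436 − 2.394 × 0.01347) / 0.01346 = 0.843; power 80%.
- 1,603 per arm: SE0 = 0.01650, SE1 = 0.01648; (0.0436 − 2.394 × 0.01650) / 0.01648 = 0.248; power 60%.

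All 16 rows of Table 2 reproduce with 2,404.5 per arm, so the table divided N by two rather than three. With 1,603 per arm every row has about 60% power. The differences that truly give 80% are 2.80 points (5% control), 5.36 (30%) and 5.70 (50%), against the stated 2.24, 4.36 and 4.66. That is a separate error; here it only fixes the starting point.

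**Why the step-down rule is valid.** Any two of the equalities together mean that all three hold. The closed family therefore contains only the global null and the three single equalities. Closed testing rejects a single equality if the global null is rejected at 5% (smallest p < 0.05 / 3) and that equality's own p < 0.05. This is Shaffer's logically restricted version of Holm for three arms. Any p below 0.01667 is still rejected, so no Bonferroni rejection can be lost.

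**Simulation.** Three binomial arms of 1,603, pooled z tests, 400,000 replicates per row. The first three columns give power for financial vs control.

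| Control / financial / social | Bonferroni | Holm | Step-down | At least one rejection (all three rules) |
|---|---|---|---|---|
| 5 / 7.24 / 5% | 0.60 | 0.63 | 0.68 | 0.76 |
| 5 / 7.24 / 7.24% | 0.60 | 0.63 | 0.68 | 0.76 |
| 5 / 7.24 / 6.12% (midway) | 0.60 | 0.61 | 0.62 | 0.63 |
| 30 / 34.36 / 30% | 0.60 | 0.63 | 0.68 | 0.76 |
| 30 / 34.36 / 34.36% | 0.60 | 0.63 | 0.68 | 0.76 |
| 30 / 34.36 / 32.18% (midway) | 0.60 | 0.61 | 0.62 | 0.63 |
| 30 / 35.36 / 35.36% (true 80%) | 0.80 | 0.83 | 0.86 | 0.91 |

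- Over control rates from 1% to 70%, the step-down figure stays between 0.675 and 0.683 when the social arm equals control or the financial arm. At 5% control and the true 80% difference it is 0.87. If the social arm has twice the effect, it is about 0.75.
- Power to show both incentives beat control, when both have the Table 2 difference: 0.44 under Bonferroni, 0.59 to 0.60 under the step-down rule.
- Family-wise error: 0.043 to 0.046 under the global null, the same as Bonferroni. With one true null left, it is rejected in 0.046 to 0.050.

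**Effect on the intervals.** A rejection gained at the second step has p between 0.01667 and 0.05. With a Wald test and Wald interval from the same model, its 98.33% odds-ratio interval always includes 1.

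**The case against.** The strongest reply is that nothing here is wrong. Bonferroni is valid, the level is stated consistently in both sections, and test decisions agree with the 98.33% intervals. Preferring a simple rule with matching simultaneous intervals is a legitimate choice. This stands in part: the point is one of efficiency. A rule that rejects everything Bonferroni rejects, and sometimes more, at the same family-wise error is still worth having when N is fixed.

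Three stronger readings are tempting, and the documents do not support them:

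- *That Bonferroni explains the shortfall from 80% to 60%.* It does not. Table 2 already uses 0.01667; the shortfall comes from dividing N by two. The step-down rule recovers at most part of it in the scenarios tabulated.
- *That power is 68% without condition.* It depends on the third arm, and the whole benefit lies in further rejections after a first one.
- *That financial vs social is an unplanned contrast that should carry no alpha.* The odds-ratio sentence names only comparisons with control. But the same section includes the contrast among its three pairwise comparisons, the Sample size section speaks of "to maintain a family-wise error rate of 0.05 across the three planned pairwise comparisons among the three conditions", and the Discussion asks which incentive is more effective. It belongs in the family.

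The objection on timing also has force. The survey closed on November 30, 2024 and the SAP is already published. Responses sit in 18 questionnaire instances labelled by arm and answer, and the research team monitored completeness during collection. The article does not show whether outcomes by arm have been seen. Relaxing two thresholds after seeing them would cost more credibility than the power is worth.

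**Conclusion.** The concern holds as an efficiency point, not as an error. At Table 2 differences the gain per comparison is about 8 percentage points in the favourable configurations and about 2 when the social arm lies midway. At differences that truly give 80% power the gain is about 6 to 7 points. The clearest benefit is for the question in objective 2 taken as a pair, at about 16 points.

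These figures assume exactly 1,603 per arm and unadjusted pooled z tests in place of the planned logistic model with residential status as covariate. The error-control argument does not depend on those choices, only on each pairwise test being valid at its own level.

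**What to change.** Replace the decision rule in the Primary outcome analysis section: test the smallest of the three p-values at 0.01667 and, only if it is significant, test each of the other two at 0.05. Base significance on adjusted p-values compared with 0.05. With ordered values p1 ≤ p2 ≤ p3, these are 3·p1 for the smallest, max(3·p1, p2) for the second and max(3·p1, p3) for the third, each capped at 1.

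Keep the 98.33% intervals for all three contrasts as simultaneous estimation intervals, and name financial vs social in the odds-ratio sentence. Amend the sentence that rests primary inference on these intervals, and state that a second-step rejection will have a 98.33% interval that includes the null. Make the same change in the SAP.

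Use the rule as primary only if the change is recorded and dated before any outcome by arm has been seen. Otherwise keep Bonferroni as primary and label the stepwise result post hoc. Correct Table 2 separately.

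The cost is a short amendment to the two documents and a reporting convention in which some significant tests and their intervals visibly disagree. No new data are needed.
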